### Participants' Enrollment

Between June 2018 and May 2019, we contacted the participants of this cohort by phone calls, and they were invited to participate in the present study. We booked those who agreed for a new application of the comprehensive geriatric and gerontological evaluation, now including the Clinical Dementia Rating (CDR) scale (47, 48) applied by a trained professional through an unstructured interview with a relative of the participant. This enabled the selection of individuals with normal cognition (CDR = 0) or mild cognitive impairment (CDR = 0.5) in the study.

The participants of the cognitive stimulation and mindfulness trial answered a specific protocol that included Montreal Cognitive Assessment (MoCA) and a questionnaire to find out what computing level they had and if they have already experienced other sorts of mediations practices on the last 6 months.

After signing the consent form, we randomly assigned study subjects to two comparative groups: intervention and control, with an allocation ratio 1:1, following the sequence of arrival in the study as shown in Figure 1.

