### Recruitment, Procedures, and Randomization

Overall, 152 elderly were recruited from the cohort of the CSR of the Universidade Federal de São Paulo from June 2018 to May 2019. Recruitment was conducted by invitation phone calls to the cohort list. Participants who showed interest in the research were scheduled to visit the center so that one of five researcher assistants would apply a comprehensive geriatric and gerontological evaluation named as Wide Geriatric and Gerontologic Assessment (WGGA), which comprise sociodemographic data and other measures' information needed for the recruitment such as GDS-15 (49–51) and baseline data such as quality of life [World Health Organization Quality of Life (WHOQOL) BREF and WHOQOL-OLD] (59–62) and ADLs, and then the MoCA (63, 64) is applied in order to evaluate cognitive function.

After this first step, a trained gerontologist applies the CDR (47, 48, 52) to evaluate if the participant has dementia or any cognitive impairment. The CDR evaluation requires a caregiver or a relative close to the older adult to be interviewed to inform about his cognition and behaviors (48). The participants who score 0 or 0.5 were included in the study.

After the screening and recruitment, the 152 participants approved in the inclusion criteria will be randomized and allocated into the groups. Married participants who meet the inclusion criteria will be allocated to the same groups; it was decided to do that because some couples need the support from one another to go to the center. The MBHP program group will then be randomized again into other four subgroups (19 participants each) because the MBI group is better availed when smaller. All the groups will follow the same assessment of the research, and the MBHP protocol will be led by instructors certified by Mente Aberta the whole time. The control group will also be randomized and allocated into small groups according to the number of computers in the computer lab (19 participants each).

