### Assessment and Outcomes

The first two assessment points (baseline, post-intervention) will occur over a week before the intervention and on the last meeting of the maintenance group, and the follow-up will occur 1 year after the last meeting of the intervention. For the baseline, the sociodemographic questionnaire, WHOQOL-BREF, WHOQOL-OLD, MoCA, and ADL questionnaire occurred during the recruitment; all the other scales will be applied a week before the intervention starts. The measures of the intervention group will be on sheets of paper as most of the participants are not familiar with using electronic devices. The typing of the data will be made by two people to supervise and to guarantee no typing mistake of the collected data. SurveyMonkey software will be used for data collection for control group as the participants will learn how to use it on the cognitive stimulation classes. All the instruments have been validated into Portuguese with reliable psychometric properties and are available in Supplementary Files (48, 49, 60, 61, 63, 65, 68, 70, 71, 73).

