### Trial Status

At the time of this manuscript submission, the recruitment for the MBHP-Elderly Study was already ongoing (started in June 2018 and predicted to finish in February 2021 with the follow-up collection).

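### The primary quality-of-life baseline is taken at recruitment, with no limit on its distance from the classes; this costs precision in changes from T0 but does not bias the comparison between arms

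*Protocol article*

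**What the plan says.** Assessment and Outcomes gives a general rule for the first two assessments: they "will occur over a week before the intervention and on the last meeting of the maintenance group". The next sentence makes an exception that covers the whole primary outcome: "WHOQOL-BREF, WHOQOL-OLD, MoCA, and ADL questionnaire occurred during the recruitment; all the other scales will be applied a week before the intervention starts". Two other sections agree with the exception. Recruitment, Procedures, and Randomization lists both WHOQOL instruments, ADL and MoCA in the screening visit, and Geriatric and Gerontologic Interview places both WHOQOL instruments in the recruitment interview. Table 2 nevertheless shows a single T0 column for every measure.

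On dates, the article says that "152 elderly were recruited from the cohort of the CSR of the Universidade Federal de São Paulo from June 2018 to May 2019". On order, it says "After the screening and recruitment, the 152 participants approved in the inclusion criteria will be randomized and allocated into the groups". Participants' Enrollment adds that assignment was made "following the sequence of arrival in the study". Trial Status has the study "predicted to finish in February 2021 with the follow-up collection". No section gives a class start date, a maximum interval from T0 to the first class, or a repeat of the WHOQOL instruments before the classes.

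Sample Size and Power Calculations bases 64 per group on differences in score relative to baseline. Statistical Analysis compares T0-T1, T1-T2 and T0-T2 differences, allows paired tests, and plans correlations between primary and secondary outcomes. It names adjustment for possible moderators but not for the T0 score.

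**The concern.** A baseline is useful for precision to the extent that it correlates with the later score, and that correlation normally falls as the gap grows. The primary outcome here has the older baseline, of an age that is not fixed and may differ between participants by about a year. Three things follow if the gap is long.

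- Change scores from T0 become noisier, and the sample size rests on change from T0.
- Change within an arm from T0 to T1 includes whatever happened between the interview and the first class, in people aged 60 or older, as well as the programme.
- The planned correlations set a primary change over one period against changes in MAAS, SCS, DASS-21, PSQI and DUREL over a shorter one. MoCA and ADL share the recruitment baseline, so the mismatch does not extend to them.

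**Working it through.** **1. The plan's own figure.** Inputs from Sample Size and Power Calculations: 64 per group, power 0.80, alpha 0.05, loss 15%. The effect size, SD and sidedness are not stated. With a two-sided two-sample t-test, 64 per group implies d = 0.499. Taking d = 0.5 gives 63.8, so 64. Then 64 / (1 − 0.15) = 75.3, so 76 per group and 152 in total. The figure reproduces, given d = 0.5.

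**2. Age of the primary T0.** Inputs: recruitment from 1 June 2018 to 31 May 2019 (month ends assumed); course of 16 weeks; T2 one year after the last meeting; T2 collection complete by February 2021. Assumption: one wave, with everyone recruited before the first class.

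- Earliest start, when recruitment closes (1 June 2019): first recruit 365 days, or 12.0 months; last recruit about 0 months.
- Latest start: end of February 2021 minus 1 year is end of February 2020; minus 16 weeks is about 9 November 2019. First recruit: 526 days / 30.44 = 17.3 months. Last recruit: 162 / 30.44 = 5.3 months.

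The five other scales are taken about a week before the start in either case.

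**3. What the T0-T1 correlation r does to power.** With equal SDs at T0 and T1, Var(change) = 2(1 − r)SD². The standardized effect is d / √(2(1 − r)) for a change score and d / √(1 − r²) with T0 as a covariate. Set d = 0.5 in units of the raw SD, 64 per arm, two-sided alpha 0.05. The values of r are assumed; the article gives none.

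| r | Power, change score | Power, adjusted for T0 |
|---|---|---|
| 0.6 | 88% | 94% |
| 0.5 | 80% | 90% |
| 0.4 | 73% | 86% |
| 0.3 | 66% | 84% |

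At r = 0.5, 2(1 − r) = 1, so the change score is no noisier than a single score and power equals the plan's 80%.

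**4. The same question with d = 0.5 on the change score.** The sample size section can also be read this way. Suppose a fresh baseline with correlation r₀ gives 80% power, and the older one lowers the correlation to r₁. The effect becomes 0.5 × √((1 − r₀)/(1 − r₁)).

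- 0.6 to 0.5: d = 0.447, power 71%.
- 0.7 to 0.6: d = 0.433, power 68%.
- 0.7 to 0.5: d = 0.387, power 59%. With adjustment for T0, power goes from 86% to 71%.
- 0.8 to 0.6: d = 0.354, power 51%.

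The direction is the same under both readings. The amount depends on the assumed correlations and on the scale of d. Nothing in the article ties a lag of so many months to a given fall in r.

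**The case against.** **The lag is inferred.** No class start date appears, and assignment by order of arrival can be read as rolling. With several waves, February 2021 dates only the last follow-up, and many gaps could be short. This stands, and the month ranges are conditional for that reason. Randomization of the 152 after recruitment, and four MBHP subgroups under four tutors on four weekdays, fit a single wave better but do not prove it. Under either reading the primary instruments lack the pre-class baseline.

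**The contradiction is mild.** The second sentence says openly which scales were taken when, and the wording of the first could mean more than a week before. This largely stands: it is loose drafting to reconcile, and the recruitment timing itself is clear.

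**A reader might infer bias between the arms.** The documents do not support that. The WHOQOL scores are taken before randomization, so the lag and any drift are balanced in expectation. This is even an advantage over the five other scales, which are handed out at the lecture where allocation is announced.

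**A reader might also infer a definite loss of power.** That is not supported either. The article gives no effect size, SD or correlation, and at r = 0.6 in raw SD units power is above plan. What stands is the direction: a baseline that correlates less with T1 makes a change score less precise.

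**Conclusion.** The point holds as one of precision and interpretation. As written, the plan lets the primary T0 be many months older than the T0 of five secondary scales, and sets no limit. On the single-wave assumption its age is 0 to 12 months at the earliest start and about 5 to 17 months at the latest. The between-arm comparison stays unbiased, and T1-T2 comparisons are unaffected.

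The effects are less precise T0-T1 and T0-T2 change scores, within-arm change that cannot be separated from drift before the programme, and correlations with MAAS, SCS, DASS-21, PSQI and DUREL over unequal periods. The illustrative power figures show how far the answer moves with r; they are not an estimate for this trial. Adjustment for T0 recovers much of any loss: at d = 0.5 in raw SD units and 64 per arm, it gives 84% to 86% at r of 0.3 to 0.4, against 66% to 73% for change scores.

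**What to change.** **Where classes have not started.** Repeat WHOQOL-BREF, WHOQOL-OLD and ADL at the pre-class session already planned for the other scales, completed before allocation is announced. Use these scores as T0 and keep the recruitment values as screening data. The cost is 26 + 24 = 50 WHOQOL items plus ADL at an existing session; the downside is more questionnaire burden for older participants. If MoCA is not repeated, say that it keeps its recruitment baseline.

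**Where classes have started.** Analyse WHOQOL-BREF and WHOQOL-OLD at T1 and T2 with the T0 score and months from T0 to class start as covariates, in place of raw change. Report that interval by arm. State that within-arm change from T0 includes time before the programme, and limit claims from correlations with the five later-measured scales. This needs no new visit, only the interview and class start dates.

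**In both cases.** Reconcile the two sentences in Assessment and Outcomes, give the class start dates, say whether there was one wave or several, and mark in Table 2 which T0 measures come from recruitment.

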Randomization will be implemented using the Microsoft Excel. Each participant will be randomized individually for each of the two groups. The couples will be stratified into the same groups as it was also considered that, if they were allocated to be separated, one could teach another what was taught and then contaminate the sample. All randomization procedures will be made by a statistical professional who will only receive the identification number of the participants and will not interact with them at any time before, during, or after the intervention.

After the randomization, the participants will be invited to attend the CSR for a lecture, which we will inform which group they were randomized to and when the intervention will start. At this moment, we will hand the participants the informed consent in written form to be signed by the interested and the measure scales that were not filled during the screening such as Mindful Attention Awareness Scale (MAAS) (65, 66), Self-Compassion Scale (SCS) (67, 68), Depression Anxiety and Stress Scale (DASS-21) (69, 70), Pittsburg Sleep Quality Index (PSQI) (71, 72), and Duke Religious Index (Durel) (73, 74).

Due to the nature of the intervention, this will be a single-blind study, in which the outcomes assessment and analyses will be blind, but the participants will be aware of their group assignment.

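### Self-completed outcomes are collected on paper in the MBHP arm and online in the control arm, so at T1 and T2 a mode effect cannot be separated from the treatment effect

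*Protocol article*

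**What the plan says.** Assessment and Outcomes ties the collection mode to the arm. For the MBHP arm: "The measures of the intervention group will be on sheets of paper as most of the participants are not familiar with using electronic devices". For the control arm: "SurveyMonkey software will be used for data collection for control group as the participants will learn how to use it". Between these two sentences stands the data-entry rule: "The typing of the data will be made by two people to supervise and to guarantee no typing mistake of the collected data".

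On baseline timing, the same section says that "WHOQOL-BREF, WHOQOL-OLD, MoCA, and ADL questionnaire occurred during the recruitment; all the other scales will be applied a week before the intervention starts". Recruitment, Procedures, and Randomization places the WHOQOL instruments within the recruitment visit, where "one of five researcher assistants would apply a comprehensive geriatric and gerontological evaluation". MAAS, SCS, DASS-21, PSQI and DUREL are handed out after randomization, at the lecture where participants learn their group.

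On blinding, that section says "the outcomes assessment and analyses will be blind, but the participants will be aware of their group assignment".

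Materials and Methods states that both groups receive the same assessment. That covers the instruments and time points and does not mention mode. The article describes no subset assessed in a common mode, no crossover of mode and no check that the two modes are equivalent. The limitations in the Discussion mention spurious effects from measurement instruments in general, but not that mode differs by arm.

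**The concern.** The primary outcome and most secondary outcomes are ratings that participants fill in themselves. Paper and web versions of such a form can differ in skipped items, response style and the share of forms returned. If everyone changed mode together, the arms would be affected alike. Here the arm decides the mode, and the reason given is that the control treatment teaches the web tool.

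A mode effect would therefore be read as an MBHP effect, or would hide one. No model can correct this afterwards, because the data contain no one in the MBHP arm on the web form and no one in the control arm on paper.

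A second, smaller matter is that a paper sheet or a SurveyMonkey export shows the arm to whoever handles it, although outcome assessment and analysis are described as blind.

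**Working it through.** **1. Which measures are affected.** These are the self-completed scales: WHOQOL-BREF, WHOQOL-OLD, MAAS, SCS, DASS-21, the self-report part of the PSQI, and DUREL. MoCA is an administered test, and the PSQI third-party items are taken by phone, so neither is affected in this way. The article does not say how the ADL questionnaire is given after baseline, so I leave it out.

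**2. Where mode enters.** Write the observed score at a post-baseline visit as true score + m × (mode), with mode = 1 for web and 0 for paper. At T1 and T2, mode = 1 exactly when arm = control. The expected difference, MBHP minus control, is then δ − m, where δ is the treatment effect. Only δ − m can be estimated.

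**3. Whether baseline helps.** WHOQOL at T0 was taken at recruitment, before allocation, so mode could not differ by arm then. The expected between-arm difference at T0 is zero. The difference in change is (δ − m) − 0 = δ − m, and m stays in full. Sample Size and Power Calculations bases the power on exactly this kind of comparison, the difference in scores relative to baseline. For the scales given after randomization, the article does not say whether control participants used the web form at T0, before their classes had begun. If they did, a constant shift would partly cancel in the change score; if not, it enters as it does for WHOQOL.

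**4. The plan's own sample size.** The article gives 64 per group for power 0.80 and α = 0.05, without an effect size, SD or sidedness. Assuming d = 0.5 and a two-sided t-test, the solution is 63.8, so 64, with power 0.801 at 64. Loss of 15%: 64 / (1 − 0.15) = 75.3, so 76 per group and 152 in total. The stated figures reproduce. The d = 0.5 is my assumption.

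**5. Illustration of size.** The documents give no m, so I assume 0, 0.1, 0.2 and 0.3 SD. With n = 64 per arm, SE = √(2/64) = 0.177 SD. The non-centrality is net difference / SE; for a net 0.2 SD it is 0.2 / 0.177 = 1.13. Rejection probabilities of the two-sided t-test at α = 0.05:

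| Assumed shift (SD) | No true effect | True d = 0.5, shift opposes | True d = 0.5, shift favours |
|---|---|---|---|
| 0 | 5% | 80% | 80% |
| 0.1 | 8.7% | 61% (net 0.4) | 92% (net 0.6) |
| 0.2 | 20% | 39% (net 0.3) | 98% (net 0.7) |
| 0.3 | 39% | 20% (net 0.2) | 99% (net 0.8) |

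A normal approximation gives nearly the same: 8.7%, 20.5% and 39.6% in the second column, and 61.9%, 39.6% and 20.5% in the third.

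**6. Blinding.** Set "The measures of the intervention group will be on sheets of paper" beside "the outcomes assessment and analyses will be blind". The raw format identifies the arm for data handlers. An analyst who receives one merged, coded file need not see it. The article neither describes such a file nor rules it out.

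**The case against.** The strongest reply is that no bias has been shown. The shifts are assumed, zero is possible, and a shift could go either way. The d = 0.5 is not in the documents either. All of this stands. The table shows how sensitive the comparison would be; it does not show that a material bias exists.

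A reader might infer that the two formats contradict the blinding statement. The documents do not support that. A merged, coded file would keep the analyst blind, and an article may leave such a step to a fuller document. For self-completed scales the rater is the participant, who is openly unblinded. What remains is a tension for those who handle source data.

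A reader might also infer that web completion at one year will fail for lack of computer skill. Control participants have 16 weeks of classes, and nothing says the forms are filled in remotely or without help, so this is speculation. Nor is it a defect that double typing seems to concern only paper, since direct electronic entry needs no transcription.

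Finally, part of the data may already exist. The article reports recruitment from June 2018 to May 2019 and expects follow-up to end in February 2021. The WHOQOL baseline cannot now be changed, and did not differ in mode by arm in any case. This limits the remedy to later assessments. It does not remove the confounding at T1 and T2.

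**Conclusion.** The point holds for the self-completed scales at T1 and T2. The article itself assigns mode by arm, and nothing in it allows a mode effect to be estimated or removed. The pre-randomization WHOQOL baseline does not help, so the primary comparison is exposed in full to whatever mode effect there is.

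The size and direction of that effect are unknown. Under assumed shifts of 0.1 to 0.3 SD with 64 per arm, the false-positive rate would be about 9% to 39%. Power against an assumed d = 0.5 would fall to between about 61% and 20% if the shift opposes the effect, and would rise to between about 92% and 99% if it favours it. These figures also assume a two-sided α of 0.05 and a constant shift. They do not cover missing data that differ by mode.

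It would go too far to conclude that the trial is biased by a known amount or that its blinding claim is false. The conclusion is that an avoidable ambiguity has been built into the main comparison and is cheap to prevent wherever data are still to be collected.

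**What to change.** **Assessments still to be collected:** use the same paper forms, in the same setting and with the same supervision, in both arms. Have the forms entered twice by staff who see only the participant's ID. The cost is typing at most about 76 more sets per time point, one for each control participant; no extra visit is needed.

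**Control data already collected online:** keep the SurveyMonkey statement in the methods, because deleting it would remove a true description of what was done. State which scales and time points were collected in which mode, including T0 for the scales given after randomization. Report mode by arm as a limitation on the primary and self-report comparisons.

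**Analysis file:** give the analyst one merged, coded file without format markers. A mode variable left in that file would duplicate the arm at T1 and T2 wherever the modes still differ. It would add no information and would unblind the analyst.

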### Geriatric and Gerontologic Interview

During the recruitment, trained professionals on the field of gerontology, nutrition, psychology, and medicine applied the WGGA developed by the CSR in order to collect sociodemographic data and evaluate the health, ADLs, chronic diseases, the drugs taken, mental health, life satisfaction, and cognitive function of the elderly. WGGA is based on the BOMFAQ (Brazilian OARS Multidimensional Functions Assessment Questionnaire) (75) in order to evaluate ADL, on the MHSQ (Mental Health Screening Questionnaire) (76) in order to evaluate mental health, and on the MMSE (Mini-Mental State Examination) (77) in order to evaluate cognitive function. The WGGA also include GDS-15 (49–51) in order to evaluate depression and WHOQOL-BREF (61) with WHOQOL-OLD (60) in order to measure quality of life. In this study, we will use GDS-15 only for inclusion criteria, in which the participants who score 7 or more will be excluded.

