## Materials and Methods

The “MBHP-Elderly Study” is a randomized controlled trial addressing older people with 3 assessment points (baseline, post-intervention, and 1-year follow-up) nested in a cohort study (the EPIDOSO study) of older adults patients assisted in a PC facility of the “Center for Aging Research” [Centro de Estudos do Envelhecimento (CEE)] of the Universidade Federal de São Paulo—UNIFESP.

One hundred fifty-two participants will be recruited from the cohort and then randomized into the following two experimental groups: (I) MBHP intervention group (76 participants) in which the elderly will have a weekly meeting of an hour and 30 min for 8 weeks to perform the MBI (MBHP protocol) accompanied by extra four 1-h meetings through a maintenance group with all participants after the eighth week (each maintenance session took place fortnightly), totaling a 4-month (16-week) intervention; (II) cognitive stimulation control group (76 participants) of elderly who will take computer-based cognitive stimulation classes for 4 months, once-a-week 1.5-h meetings without maintenance phase, totaling 16 weeks. In both groups, the same assessment for data collection will be applied, and they will be applied in the baseline (T0), post-intervention (T1), and 1-year follow-up (T2). Both interventions will last 16 weeks. However, the reason why the MBHP intervention group will take 12 sessions and the cognitive stimulation control group 15 sessions is because one of the aims in the MBHP intervention is to work on the participants' autonomy in their personal mindfulness practice in daily life through home activities exercises, and we wanted to compare its outcomes with the 4-month weekly meetings of control intervention, which require face-to-face sessions. Study design and participant flow through the trial is shown in Figure 1.

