### Statistical Analysis

All analyses will be conducted using intention-to-treat and per-protocol analyses following the CONSORT recommendations for reporting the results (44).

Categorical variables will be described by absolute and relative frequencies. Numerical variables will be checked for their distributions through histograms and boxplots. If considered as having normal distribution, they will be described by mean and standard deviation. Otherwise, they will be described by medians and quartiles.

The primary outcome of this study is the quality of life measured by the WHOQOL-BREF and WHOQOL-OLD, and the secondary outcomes are cognitive function measured by the MoCA, level of consciousness at present measured by the MAAS, self-compassion measured by the SCS, Psychological Health measure by DASS-21, sleep quality measured by PSQI, and religiosity assessed by the Duke University Religion Index. Sociodemographic questions (sex, age, schooling), treatment group, and time will be the independent variables.

To verify the homogeneity between the study groups regarding sociodemographic measures at the initial time of the study, the groups will be compared by means of hypothesis tests of the type: χ^2^ and/or Fisher exact for categorical variables and multivariate analysis of variance (MANOVA) and/or Kruskal–Wallis for numerical or ordinal variables. A descriptive analysis of the sociodemographic categories regarding the sex, age, and schooling of both groups will be carried out.

Measures of preintervention (T0), post-intervention (T1), and follow-up (T2) outcomes may be compared by means of MANOVA for repeated measures. If necessary, Student *t*-tests will be conducted for paired or Wilcoxon data by applying corrections by the Holm or Bonferroni method. A Pearson correlation coefficient analysis will also be performed between the means of the primary outcomes and those of the secondary outcomes to examine the degree of changes in the outcome measures over time.

The difference between the measures T0 to T1, T1 to T2, and T0 to T2 can be compared between the intervention groups in MANOVA of repeated measures by means of Mann-Whitney tests. If necessary, these models will also be adjusted to assess the effects of time and intervention group, controlling for possible moderating variables.

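### Baseline WHOQOL was taken inside a staff-applied evaluation but later scores come on paper or SurveyMonkey by arm, so control-arm changes from T0 almost certainly cross modes and MBHP-arm changes probably do

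*Protocol article*

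**What the plan says.** **Baseline.** The section Geriatric and Gerontologic Interview says that "trained professionals on the field of gerontology, nutrition, psychology, and medicine applied the WGGA developed by the CSR" and that "The WGGA also include GDS-15 (49–51) in order to evaluate depression and WHOQOL-BREF (61) with WHOQOL-OLD (60) in order to measure quality of life". Recruitment, Procedures, and Randomization agrees that "one of five researcher assistants would apply a comprehensive geriatric and gerontological evaluation" at the centre visit, and puts randomization after this step. Assessment and Outcomes confirms the timing: "For the baseline, the sociodemographic questionnaire, WHOQOL-BREF, WHOQOL-OLD, MoCA, and ADL questionnaire occurred during the recruitment".

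**Collection by arm.** The same section says: "The measures of the intervention group will be on sheets of paper as most of the participants are not familiar with using electronic devices". The control arm uses SurveyMonkey, on the ground that its participants will be taught it in the computer classes. Table 2 schedules both WHOQOL instruments at T0, T1 and T2. The article describes no repeat of the recruitment evaluation.

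**Common assessment.** Materials and Methods says: "In both groups, the same assessment for data collection will be applied", and applies this to all three visits. It names no common mode.

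**Use of the baseline.** Sample Size and Power Calculations compares the two groups on mean differences relative to baseline. Statistical Analysis compares T0–T1, T1–T2 and T0–T2 differences between groups, and adds: "If necessary, Student *t*-tests will be conducted for paired or Wilcoxon data".

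**The concern.** A change score is clean only if both scores are obtained in the same way. If staff ask the questions at T0 and the participant answers alone on paper or screen later, the change contains any systematic difference between the modes as well as true change.

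The primary outcome is at stake. The Introduction hypothesises both that MBHP promotes quality of life and that it is superior to cognitive stimulation. Paired tests of change from T0 within the MBHP arm could be read as support for the hypothesis that MBHP promotes quality of life, and a mode shift could produce or hide such a change. Between arms the question is different: which part of the mode effect survives the randomized comparison?

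**Working it through.** **1. The plan's own figure.** The article states 64 per group, power 0.80 and α 0.05, but no effect size or sidedness. A two-sided two-sample t-test with an assumed d = 0.5 gives power 0.801 at 64 per group. Allowing for 15% loss, 64 / 0.85 = 75.3, rounded up to 76 per group and 152 in total. The stated figures reproduce, and none is wrong on this point.

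**2. Is there a mode change?**

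| Arm | T0 | T1/T2 | Mode change |
|---|---|---|---|
| Control | Before randomization, in the staff-applied evaluation | SurveyMonkey, learned in class | Almost certain, whoever held the pen at T0 |
| MBHP | Same as control | Paper | Only if T0 was an interview and T1/T2 are self-completed: natural reading, not stated |

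**3. Which part reaches which comparison?** Let I, P and S be the additive effects of the baseline mode, paper and SurveyMonkey.
- Within MBHP, change from T0 is biased by P − I.
- Within control, it is biased by S − I.
- Between arms, the bias is (P − I) − (S − I) = P − S.

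The baseline mode drops out between arms on either reading of the T0 procedure. The paper-versus-SurveyMonkey difference stays, because it coincides with arm. T1–T2 change within an arm involves no mode switch, provided that arm keeps its mode.

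**4. Size within an arm.** The documents give no mode effect and no T0–T1 correlation, so both are assumptions. Take n = 64 and no true change. For a shift δ in SD of the score, the SD of change is √(2(1 − r)), and the noncentrality of the paired t-test (63 df, two-sided 0.05) is δ√64 / √(2(1 − r)). With r = 0.6 the SD of change is √0.8 = 0.894.

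| δ (SD of score) | Noncentrality | P(declared significant) |
|---|---|---|
| 0.1 | 0.8 / 0.894 = 0.89 | 0.14 |
| 0.2 | 1.6 / 0.894 = 1.79 | 0.42 |
| 0.3 | 2.4 / 0.894 = 2.68 | 0.75 |

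For δ = 0.2 the probability is 0.35 at r = 0.5 and 0.53 at r = 0.7.

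**5. Size between arms.** For an assumed P − S of 0.05, 0.1, 0.2 or 0.3 SD of change, 64 per arm and no true effect, the two-sample t-test rejects with probability 0.059, 0.087, 0.202 or 0.392. With a true d = 0.5, a differential shift of 0.1 SD moves power from 0.80 to 0.61 if it works against MBHP, or to 0.92 if it works in its favour.

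**6. Power through a lower correlation.** Hold the raw effect at 0.5 × √0.8 = 0.447 SD of the score. If the mode switch lowered r from 0.6 to 0.5, the standardized effect would be 0.447 / √1.0 = 0.447 and power 0.71. At r = 0.4 it would be 0.447 / √1.2 = 0.408 and power 0.63. Nothing in the documents shows that r would fall.

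**The case against.** The strongest objection is that the article never says the WHOQOL was read aloud at T0 or self-completed later. The inference rests on a section heading and on the verb used for delivering the evaluation. Assessment and Outcomes uses that verb for scales which Recruitment, Procedures, and Randomization hands to participants, and the latter section speaks of scales being filled in at screening. Paper is a medium and does not identify who writes on it. The follow-up battery includes the MoCA, which cannot be self-completed unaided, so assessors may be present at T1 and T2. This stands for the MBHP arm: if T0 was filled in on paper, that arm has no mode change. It does not remove the control-arm change, because the T0 scores predate both randomization and the SurveyMonkey teaching.

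A reader might infer that every T0-based quality-of-life comparison is contaminated. The documents do not support that: the MBHP change is not established, and a common additive baseline effect cancels from the between-arm comparison on which the trial is sized. A reader might also infer that the trial has less power than stated. That holds only under an assumed fall in correlation.

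The paired tests are planned only if needed, and uncontrolled within-arm change is weak evidence of efficacy in any mode. That lowers the stakes but is no reason to leave the mode undefined. The Discussion's remark on response styles concerns correlations among items measured by common methods, so it neither supports nor answers this point.

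**Conclusion.** The concern holds in a limited form. The primary outcome almost certainly changes mode between T0 and T1/T2 in the control arm, and on the natural but unstated reading in the MBHP arm too. Within-arm changes from T0 are then not interpretable as true change alone. The false-positive probabilities of 0.14 to 0.75 depend on an assumed shift of 0.1 to 0.3 SD, an assumed correlation of 0.6 and 64 completers.

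The randomized comparison is not biased by a baseline mode that both arms share, if its effect is additive. It is exposed to the paper-versus-SurveyMonkey difference at T1 and T2, whose size is unknown. Any loss of power from a lower correlation is conditional. No sample-size figure needs to change.

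**What to change.** 1. State, for each visit and arm, how WHOQOL-BREF and WHOQOL-OLD are completed: who reads the questions, who records the answers, and in what medium.
2. Use the same paper form in both arms at T1 and T2. For anyone not yet assessed, use it at T0 as well, before the arm is announced.
3. Where only the score from the recruitment evaluation exists, use it as a baseline covariate in the between-arm comparison of T1 and T2 scores.
4. Do not report within-arm T0–T1 or T0–T2 WHOQOL changes as evidence of efficacy.

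The cost is some data entry for the control arm, 26 + 24 = 50 more items for anyone re-assessed at T0, and the loss of within-arm change claims. The article reports recruitment from June 2018 to May 2019, so a new T0 form may come too late for many or all participants. Steps 1, 3 and 4 remain open, as does the common form at visits still to come. Where scores were already collected by arm-specific mode, mode cannot be separated from arm, and the report should say so.
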